## Abstract

**Background:**

Recovery after stroke is dependent on how much time can be spent on rehabilitation. Recently, we found that therapy time for older stroke patients on a rehabilitation unit of a nursing home could be increased significantly from 8.6 to at least 13 hours a week. This increase was attained by the implementation of interventions, focused on strength, mobility and balance. Nurses carried out these exercises with the patients during their daily activities. The aim of the present study is to investigate if increased therapy time has a positive effect on cognition, mood (depression and anxiety), and ADL in stroke patients.

**Methods:**

A comparative single blind controlled study will be applied. Patients suffering from a stroke and staying on one of the rehabilitation units of the nursing homes are eligible for participation. Participants belong to the intervention group if they stay in two nursing homes where four interventions of the Clinical Nursing Rehabilitation Stroke Guideline were implemented. Participants who stay in two nursing homes where therapy is given according to the Dutch stroke Guideline, are included in the control group. Clinical neuropsychologists will assess patients’ cognitive functioning, level of depression (mood) and anxiety. Nurses will assess a Barthel Index score on a weekly basis (ADL). These variables are measured at baseline, after 8 weeks and at the moment when participants are discharged from the nursing home.

**Discussion:**

The present study evaluates the effect of increased therapy time on cognition, mood (level of depression and anxiety), and ADL in stroke patients. When positive effects will be found this study can guide policy makers and practitioners on how to implement more therapy time on rehabilitation wards of nursing homes.

**Trial registration:**

TNR Our study has been documented in the Dutch Trial Registration, TC = *3871*.

## Background

Recovery from stroke is highly dependent on intensive therapy executed by a multidisciplinary team [1-7]. Surprisingly, in a previous study we found that time spent on non-therapeutic activities accounted for 80% of the daytime, of which 28% was spent on sitting [8]. These undesirable results are supported by other studies examining the amount of time a patient actively participates in rehabilitation on a stroke unit and in hospitals [9-15]. In a recent study we showed that therapeutic activities at a rehabilitation unit of a nursing home can be increased with more than 50 minutes a day when nurses built in exercises during their daily routines [16]. In this way patients perform 50% more therapeutic activities during the day compared to what is prescribed by the Dutch Stroke Guidelines [17].

There is ample evidence that exercise has a beneficial influence on, among others, cognitive functions, in older persons without dementia [18].

Cognitive functions that respond positively to exercise are executive functions in particular [19]. Executive functions include higher-order cognitive functions such as planning, set-shifting, attention, impulse control, and working memory [20]. A prerequisite is that these older persons are sedentary at the beginning of the exercise program [21]. There is a limited number of studies showing improvement of cognitive functioning in stroke patients as a consequence of exercise. Some cognitive domains related to motor learning, e.g. information processing speed and attention improved by aerobic exercise post stroke [22,23]. It is interesting to know if other impaired domains of cognition in stroke patients can be influenced by exercise, e.g. executive functions and memory as particularly these functions are crucial for independent functioning [24].

The question arises whether an increase in exercise time of approximately 50 minutes a day is sufficient to have a beneficial influence on cognition, e.g. executive functions, and mood in frail stroke patients. It is known that a decline in cognition and mood both relate to more severe functional limitations and less functional recovery [25,26]. More specifically, the prevalence of cognitive disorders in stroke patients is high and varies from 22% [27] to 63% [28]. It has been observed that cognitive impairment after stroke influences recovery of functional outcome and activities of daily living negatively in older stroke survivors [29,30]. Concerning mood, the frequency of e.g. depression after stroke is also high (33%) [31]. Depressed patients have poorer recovery patterns and need more time to achieve a high level of independence [32]. Moreover, stroke patients who could not successfully being discharged from nursing homes were more depressed [33].

In sum, the primary goal of the present study is to investigate whether an increase in therapy time has a beneficial influence on the various dimensions of cognition of frail stroke patients at discharge of rehabilitation units of nursing homes. The secondary goal is to examine whether an increase in therapy time improves mood, resulting in an improvement in activities of daily living (ADL).

## Methods

### Study design

The design of the study is a single blind controlled trial with two patients groups coming from nursing homes with two different rehabilitation approaches. The study consists of an effect evaluation and will be carried out in four nursing homes in the Netherlands. In the two control nursing homes, rehabilitation is only performed by therapists and based on the Dutch Stroke Guidelines [17]. Consequently, therapy time will be limited. In two intervention nursing homes, exercises derived from the Clinical Nursing Rehabilitation Stroke Guideline [34], are an additional part of the rehabilitation program, resulting in an extra 50 minutes a day of exercises for the patients.

The Medical Ethical Committee of the Free University Amsterdam, The Netherlands, approved this study.

### Study population

Patients suffering from a stroke will be eligible for participation, even if they suffer from co-morbid diseases such as heart disease, recurrent stroke or pre-existing depression. Patients will be excluded if they will leave the rehabilitation unit within two weeks, when they are too ill to participate, if there is a language problem, like aphasia, or when a Mini-Mental State Examination (MMSE) [35] score is lower than 13. A score of 13 or higher is a prerequisite for a neuropsychological assessment. Patients will be recruited by the head of the nursing staff, working on the rehabilitation unit of the nursing homes. Oral and written information about the study is given to the patients and/or their legal representatives. Prior to their participation in the study oral and written informed consent will be acquired from all the participants, their family or legal representatives. Informed consent will be based on veracity, anonymity, privacy, and confidentiality.

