### Randomisation

A convenience sample will be taken of patients who rehabilitate in the selected nursing homes in the period of April 2012 until April 2015 and are willing to participate.

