### Single-blind

The nursing homes, patients, caregivers, and the multidisciplinary teams who are participating in the study are not blinded for the treatment. Trained clinical neuropsychologists, collecting the data, do not belong to the permanent staff of the nursing homes and are not informed about the study objectives. Research assistants involved in the data analyses are blinded for the patients treatment background.

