### Data-analysis

Descriptive analysis on all the patient characteristics at baseline is performed. A t-test for independent groups will be used to check for comparability between the intervention and control group at baseline. A repeated-measures multivariate analysis of variance (MANOVA) will be applied to assess possible effect of increased therapeutic time over various test moments (baseline, 8 weeks and at the moment of discharge). The level of significance is 0.05. The SPSS-PC version no. 20 will be used for data-analyses (SPSS Inc., Chicago, IL, USA).

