## Discussion

The present protocol paper describes the design of a single blind controlled trial. The aim of our study is to investigate whether additional therapy time focused on muscle strengthening, sitting balance and reach, getting up from a chair and walking has a positive effect on cognition, mood and activities of daily living (ADL) in stroke patients who rehabilitate on rehabilitation units of nursing homes. The study gives insight into how the care of elderly stroke patients in nursing homes might be improved so that patients have a better chance of independent living. When positive effects will be found this study can guide policy makers and practitioners on how to implement higher quality care on rehabilitation wards of nursing homes.

The strength of the study is that 1) interventions from the evidence based Clinical Nursing Rehabilitation Stroke Guideline are implemented in the rehabilitation care of older stroke patients. This implementation will significantly increase the time spent on therapeutic activities without extra therapists needed, 2) the role of nurses can shift towards a more therapeutic one, 3) we examine if an increase in therapeutic time has a beneficial effect on cognition, mood, and ADL. These factors are of great importance for rehabilitation success in stroke patients. Possible limitations of our study are 1) the high rate of drop-out due to illness or death of this frail patient group, 2) the convenience sample causing a possible selection bias, 3) the limited intervention time before patients are discharged from the rehabilitation units.

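### With the arm known by home and an unblinded head nurse recruiting a convenience sample, selection within homes can differ between arms; consecutive enrolment would limit it cheaply

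*Protocol article*

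**What the plan says.** The abstract's Methods paragraph fixes the arm by place of stay: "Participants belong to the intervention group if they stay in two nursing homes" that have implemented the nursing exercises. Patients in two other homes form the control group. Under Study population, "Patients will be recruited by the head of the nursing staff, working on the rehabilitation unit of the nursing homes". The sampling rule stands under the heading Randomisation, although nothing is randomised: "A convenience sample will be taken of patients who rehabilitate in the selected nursing homes in the period of April 2012 until April 2015", provided that they are willing. Under Single-blind, "The nursing homes, patients, caregivers, and the multidisciplinary teams who are participating in the study are not blinded for the treatment". Only the assessing neuropsychologists are kept uninformed of the objectives, and only the research assistants who analyse the data are blinded to treatment.

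The Discussion lists as a limitation "the convenience sample causing a possible selection bias". On comparability of the groups, Data-analysis says: "A t-test for independent groups will be used to check for comparability between the intervention and control group at baseline". It attaches no consequence to the result.

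**The concern.** When allocation cannot be concealed, the main protection against selective entry is a rule that leaves the recruiter little choice about whom to invite. Here the recruiter knows the arm in advance, and the stated sampling rule does not require every eligible patient to be invited. If the mix of invited patients differs between intervention and control homes, the arms can differ in prognosis for reasons unrelated to therapy time. That could produce, hide or inflate a difference in cognition, mood or ADL.

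This comes on top of the larger problem that homes, two per arm, are not randomised. Unlike that problem, it can be reduced without changing the design. A baseline t-test sees only what is recorded. The characteristics listed under Patient characteristics and Medical history data do not include motivation or the recruiter's view of a patient's prospects.

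**Working it through.** No figure in the plan depends on this point, so there is none to reproduce. The check has three parts.

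**1. The text.** Arm set by home (abstract, Study design), recruiter on the unit (Study population), no blinding of homes or teams (Single-blind) and convenience sampling (Randomisation) together mean that entry is neither concealed nor consecutive. Some exclusions also need judgement: "when they are too ill to participate" has no criterion attached, and leaving within two weeks has to be predicted.

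**2. Possible size.** Enrolment shares and correlations below are assumptions; the documents give none. If a home enrols the top share p of eligible patients on a normally distributed judgement that correlates c with outcome, the mean outcome shifts by c × φ(z)/p SD, where z cuts off the top share p.

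- p = 0.6: φ(z)/p = 0.386/0.6 = 0.644.
- p = 0.8: φ(z)/p = 0.280/0.8 = 0.350.
- Difference between arms at c = 0.3: 0.3 × (0.644 − 0.350) = 0.088 SD.
- Range: 0.7 against 0.8 at c = 0.2 gives 0.029 SD; 0.5 against 0.7 at c = 0.5 gives 0.151 SD.
- A more extreme case: one arm leaves out the worst 10% to 30%, the other leaves out nobody, and the correlation is 0.3 to 0.7. This gives 0.06 to 0.35 SD.

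All of these are shifts in outcome level at a single time point. For scale, the planned effect is d = 0.30 (Sample size).

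The planned analysis is a repeated-measures MANOVA over baseline, 8 weeks and discharge, so the level shift has to be carried through to a change or baseline-adjusted contrast. Take the central 0.088 SD, with c = 0.3 at both baseline and follow-up and equal SDs:

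- Change from baseline, or group by time: 0.088 − 0.088 = 0.
- Adjustment for baseline with baseline–follow-up correlation ρ: 0.088 × (1 − ρ). At ρ = 0.7 this is 0.026 SD; at ρ = 0.5 it is 0.044 SD (ρ assumed).
- If judgement correlates 0.3 with follow-up but not with baseline, so that selection is on recovery alone, the whole 0.088 SD remains.

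**3. Burden of the fix.** Planned recruitment is 81 per group, 162 in all. Over 4 homes and 3 years, 162/(4 × 3) = 13.5 enrolments per home per year, about one a month.

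**The case against.** Several stronger readings are tempting, and the documents do not support them.

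- **That the head nurse hand-picks patients.** The article says recruited, not chosen. The Randomisation section could even mean all willing eligible patients in four conveniently selected homes. What stands is that the stated rule allows selection and the recruiter knows the arm.
- **That intervention homes have a one-sided incentive to enrol fitter patients because of the 10 to 20 extra exercise moments a day.** Study design presents the exercises as part of the homes' rehabilitation programme, so patients there appear to receive them whether or not they are enrolled. The Experimental group section says they are adapted to each patient's level. Enrolment then adds mainly testing, which is the same in both arms. No direction of bias can be claimed.
- **That the bias is about 30% of the planned effect.** 0.088/0.30 does give 29%, but this sets a level shift against an analysis that uses the baseline measurement. Baseline cognition, mood and Barthel score absorb much of prognosis. Only selection on recovery itself survives in full.
- **That the absence of a screening log is an error.** A journal article may leave a log to the full protocol, so this is not counted as a defect. Convenience sampling is different: it is the stated design.

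It can also be said that the authors disclose the bias. They do, but the article's only related step is the baseline t-test, which does not limit selection. Finally, the fix keeps the same unblinded recruiter and the judgement-based exclusions, and the documents give no admission numbers or tester capacity from which to prove that it is cheap. Both points stand as limits on what the fix achieves and on how firmly its cost can be stated.

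**Conclusion.** The point holds as a worthwhile, inexpensive improvement to a stated design choice. Because the arm is known by home, the recruiter is unblinded and the sample is one of convenience, selection within homes can differ between arms in an unknown direction.

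Under the assumed 60% against 80% enrolment and correlation 0.3, the outcome level shifts by about 0.09 SD. In a change or baseline-adjusted analysis this becomes 0 to about 0.04 SD if selection acts equally on baseline and follow-up, and more only if it acts on recovery. These sizes rest wholly on assumed shares and correlations. They show what is possible, not what will occur.

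**What to change.** In the Randomisation section, replace the convenience sample with consecutive enrolment. Every stroke admission to the four units in the recruitment period is checked against the Study population criteria, and all who qualify are invited until the planned number is reached. The same head nurse keeps a brief log of patients screened, invited and enrolled, with reasons for non-enrolment. The enrolled share is reported per home.

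At about one enrolment per home per month, this should need no extra staff, and it leaves the planned sample size, the tests and the intervention unchanged. The cost is a little paperwork and ethics wording for minimal data on non-participants.

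The change limits recruiter selection and makes it visible. It does not remove differences between homes, differences in who consents, or the discretion left in the judgement-based exclusions, and the report should say so.

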### Randomisation

A convenience sample will be taken of patients who rehabilitate in the selected nursing homes in the period of April 2012 until April 2015 and are willing to participate.

### Single-blind

The nursing homes, patients, caregivers, and the multidisciplinary teams who are participating in the study are not blinded for the treatment. Trained clinical neuropsychologists, collecting the data, do not belong to the permanent staff of the nursing homes and are not informed about the study objectives. Research assistants involved in the data analyses are blinded for the patients treatment background.

### Sample size

The sample size has been calculated by using the statistically power analysis program G Power. The estimated effect-size comes from a study reporting the effect of physical activity on cognition in patients with stroke (*d’* = 0.30) [27]. Taking into account a type one error of 0.05 (α = 0.05), a power of 0.80 (β = 0.08), three repeated measurements and two groups, a sample size of 138 patients is required, i.e. 69 persons in each group. Taken a dropout of 10% into account, a sample size of 81 persons in each group is required.

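### The nursing home determines the group (two homes per arm), but the sample size and the MANOVA treat patients as independent; if outcomes vary between homes, the 5% level and the 80% power do not hold

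*Protocol article*

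**What the plan says.** The abstract of the protocol article sets the group by place of stay: "Participants belong to the intervention group if they stay in two nursing homes" that implemented the nursing guideline, and "Participants who stay in two nursing homes where therapy is given according to the Dutch stroke Guideline, are included in the control group". Study design confirms that the work "will be carried out in four nursing homes in the Netherlands". Under Randomisation there is no allocation procedure: "A convenience sample will be taken of patients who rehabilitate in the selected nursing homes".

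The Sample size section lists its inputs: an effect size of 0.30, alpha 0.05, power 0.80, three repeated measurements, two groups and 10% dropout. From these it concludes that "a sample size of 138 patients is required, i.e. 69 persons in each group", raised to 81 per group for dropout. The number of homes, an ICC and a design effect are not among the inputs.

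Data-analysis states: "A repeated-measures multivariate analysis of variance (MANOVA) will be applied to assess possible effect of increased therapeutic time over various test moments". The significance level is 0.05, and no home term is named. The limitations in the Discussion include selection bias from the convenience sample, but not clustering or differences between homes.

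**The concern.** Each home's own nurses deliver the extra exercises and coordinate their weekly adjustment (Experimental group). Nursing staff also score the Barthel Index (Procedure). Patients in one home may therefore progress more alike than patients in different homes. If so, 69 patients per arm carry less information than 69 independent patients. The treatment contrast then has to be judged against variation between homes, for which four homes in two groups leave 4 − 2 = 2 degrees of freedom.

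A patient-level analysis ignores this. Its standard error is too small, and an ordinary difference between two pairs of homes can reach p < 0.05 and be read as an effect of therapy time. The Discussion expects positive results to guide policy makers and practitioners, so a false positive on the primary cognitive outcomes would matter.

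**Working it through.** **Inputs from the article.** Two homes per arm (Abstract, Study design); 69 analysed patients per arm, alpha 0.05, power 0.80, effect size 0.30, three measurements, two groups (Sample size).

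**Assumptions.** ICC of 0.01, 0.02 or 0.05 for the outcome analysed, since the article gives none. Equal homes, so 69 / 2 = 34.5 analysed patients per home, since the article gives totals per group only. Two-sided tests, since the sidedness is not stated.

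**Step 1: the plan's own figure.** 138 could not be reproduced from the stated inputs.
- A plain two-group comparison at 0.30 needs 175 per arm two-sided (350 in total) or 138 per arm one-sided (276 in total). With 69 per arm, two-sided power is 42%.
- A repeated-measures calculation with f = 0.30 / 2 = 0.15 and a correlation of 0.5 between measurements needs 236 in total for the between-group effect, or 74 to 76 for the group-by-time interaction.
- With f = 0.15, a total of 138 appears only at a correlation of about 0.05 to 0.08. It also appears in a global MANOVA with f² = 0.09 and four responses, not three.

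The correlation and the effect tested are not stated, so 138 is unreproducible rather than shown to be wrong. None of these variants allows for clustering. The steps below therefore take 80% under independence as given and measure the loss from it.

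**Step 2: formulas.**
- Design effect: DE = 1 + (34.5 − 1) × ICC
- Effective patients per arm: 69 / DE
- True type I error of the patient-level test: 2 × [1 − Φ(1.96 / √DE)]
- Noncentrality: (1.96 + 0.84) / √DE = 2.80 / √DE
- Power after the design effect: Φ(2.80 / √DE − 1.96)
- Power of a home-level test: noncentral t with 2 df, critical value 4.303

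**Step 3: results.**

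| Assumed ICC | DE | Effective n per arm | Type I error | Power, DE only | Power, 2 df |
|---|---|---|---|---|---|
| 0 | 1.00 | 69 | 5% | 80% | 35% |
| 0.01 | 1.34 | 52 | 9% | 68% | 28.7% |
| 0.02 | 1.67 | 41 | 13% | 58% | 24.5% |
| 0.05 | 2.68 | 26 | 23% | 40% | 17.7% |

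Example at 0.05: DE = 1 + 33.5 × 0.05 = 2.675; 1.96 / √2.675 = 1.198; 2 × [1 − Φ(1.198)] = 0.231. A simulation of 40,000 trials with two homes per arm gave type I errors of 9.2%, 12.9% and 23.4%, in agreement with the formula.

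**Step 4: would more patients in the same homes help?** Patients per home needed for an effective 69 per arm: 69 × (1 − ICC) / (2 − 69 × ICC). This gives 52 at ICC 0.01 and 109 at 0.02. At 2 / 69 = 0.029 or above the denominator is zero or negative, so no number of patients in two homes per arm is enough.

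**Step 5: would a random home effect suffice?** The home variance is estimated at zero when the between-home mean square falls below the within-home one. For four equal homes the probability is P[F(2, 134) < 1 / DE]: about 53%, 45% and 31% at ICC 0.01, 0.02 and 0.05. The model then reverts essentially to the patient-level standard error, and in common Satterthwaite implementations to patient-level degrees of freedom.

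**The case against.** **The size is conditional.** The article gives no ICC. The planned analysis runs over three time points including baseline, and its natural effect is group by time. Stable differences in level between homes cancel there, so the relevant ICC is that of change, which may be smaller than that of the scores. This stands. It makes the figures illustrative, and only an ICC of exactly zero keeps the nominal values.

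**An article condenses.** Model terms are often left to an analysis plan, so the missing home term is the weaker half of the evidence. But the Sample size section lists its inputs and states a required number. A later mixed model would leave that power statement uncorrected.

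**Readings that go too far.**
- A reader might infer that patients in one home share testers, case mix and discharge policy. The Single-blind section says only that the neuropsychologists are outside the homes' permanent staff. Procedure ties discharge to the patient's condition and personal situation. Case mix by home is not described. Shared nursing staff is the inference that the text supports.
- A reader might take 68%, 58% and 40% as this trial's power. They are losses from an 80% base that could not be reproduced.
- A reader might speak of homes being assigned to treatment. Nothing is allocated by a stated procedure; the home simply determines the group.
- A reader might expect a random home effect to repair the design. With four homes it often would not change the result, and it cannot separate treatment from home.

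**Conclusion.** The concern holds in conditional form. The stated 80% power and the nominal 5% level assume independent patients, in a design where two homes make up each arm. If change over time varies between homes at all, the patient-level test rejects too often and the power is below the stated value. At an assumed ICC of only 0.01 the type I error nearly doubles, to about 9%; at 0.05 it is about 23%. This rests on the assumed ICC range, equal home sizes and a two-sided comparison standing in for the MANOVA.

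The limit of 2 degrees of freedom does not depend on the ICC: even at ICC 0, a home-level test has about 35% power for an effect that patient-level analysis would detect with 80%. Treatment is also largely confounded with home, which neither more patients nor a cluster term can cure. The documents do not establish that the ICC is above zero, nor how large it is. They do establish that the plan makes no stated allowance for it and does not list it as a limitation.

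**What to change.** 1. **Sample size.** State that 80% power assumes independent patients with no home effect, and give the power over a range of ICC values. State the test and the correlation between measurements behind 138, so that the base figure can be checked.
2. **Data-analysis.** Beside the MANOVA, report the four home-specific adjusted changes and a home-level comparison on 2 degrees of freedom. If a mixed model with a random home effect is used, fix the denominator degrees of freedom at the home level (2), so that a zero variance estimate does not return the model to patient-level degrees of freedom.
3. **Discussion.** Add clustering and home-level confounding to the limitations. Word the conclusion as a comparison of two pairs of homes, and do not claim a therapy-time effect from the unclustered p-value alone.

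Cost: changes to text and analysis code, with no more patients. The price is a much less favourable power statement, wider intervals (the multiplier alone rises from 1.96 to 4.303, a factor of about 2.2) and a conclusion that is more exploratory than the article now implies.

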#### Rivermead behavioural memory test

Episodic memory will be tested by the Rivermead Behavioural Memory Test (RBMT) Face and Picture Recognition [41]. The Face Recognition subtest is meant to assess nonverbal episodic memory; the Picture Recognition subtest is meant to assess both verbal and nonverbal episodic memory. The RBMT has reliability coefficients ranging from 0.57 to 0.86, with the inter scorer reliability of the RBMT being 0.9 or higher. The maximum score of the Face Recognition subtest is 10. The maximum score of the Picture Recognition subtest is 20 [41].

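### The sample-size paragraph contradicts itself: 69 per group with 10% dropout gives 77 per group, not 81, and power of 0.80 means beta of 0.20, not 0.08

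*Protocol article*

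**What the plan says.** All the figures are in the Sample size section of the protocol article. The calculation was done in G*Power for "three repeated measurements and two groups". The effect size is taken from a cited study of "the effect of physical activity on cognition in patients with stroke (*d’* = 0.30"). The error rates are a type one error of 0.05 and "a power of 0.80 (β = 0.08"). The result is 138 patients, 69 in each group. The last step adds attrition: "Taken a dropout of 10% into account, a sample size of 81 persons in each group is required".

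The Discussion lists among the study's possible limitations "the high rate of drop-out due to illness or death of this frail patient group", without giving a rate. The Data-analysis section plans a repeated-measures MANOVA over baseline, 8 weeks and discharge.

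**The concern.** Two statements in one short paragraph cannot be true together with the figures beside them. The recruitment target does not come from the evaluable number and the dropout rate printed with it, and the beta does not belong to the power printed with it.

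The target of 81 is what the trial recruits to, and 10% is the attrition it says it can absorb. If they do not match, a reader cannot tell which loss was planned for, and anyone monitoring recruitment or retention has two incompatible benchmarks. The beta and power pair is the paragraph's only statement of the type two error. Read literally, it leaves open whether 80% or 92% power was intended.

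**Working it through.** **Inputs (Protocol article, Sample size):** 69 per group, 138 in total; dropout 10%; target 81 per group; power 0.80; beta 0.08; alpha 0.05, sidedness not stated; d = 0.30; three measurements; two groups.

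**1. Dropout.** I tried to reproduce 81 from 69 and 10%:

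| Method | Calculation | Per group |
|---|---|---|
| Divide by proportion retained | 69/0.90 = 76.7 | 77 |
| Simple multiplication | 69 × 1.10 = 75.9 | 76 |
| 10% applied twice, division | 69/0.90² = 85.2 | 86 |
| 10% applied twice, multiplication | 69 × 1.10² = 83.5 | 84 |

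None gives 81. Working backwards, 81 enrolled and 69 retained is a loss of 1 − 69/81 = 14.8%. As a mark-up it is 81/69 − 1 = 17.4%. A loss of exactly 15% would give 69/0.85 = 81.2, or 82 if rounded up, so 81 is best described as allowing for just under 15%.

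Difference from the correct figure: 81 − 77 = 4 per group; 162 − 154 = 8 in total. If loss really were 10%, 81 would leave 81 × 0.90 = 72.9 per group against the 69 required.

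**2. Beta.** Beta = 1 − power = 1 − 0.80 = 0.20. A beta of 0.08 would be power of 0.92. The two are not interchangeable: for a plain two-sided comparison of two means at d = 0.30, 80% power needs 175 per group and 92% needs 252.

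**3. Can 138 be checked? (secondary)** A repeated-measures sample size depends on the within-patient correlation ρ, on which effect is tested, and on how d is turned into the effect size f that the routine takes. The article gives none of these. Two readings show how much this matters.

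*Reading A: f = d/2 = 0.15 entered directly, with m = 3 measurements.* The noncentrality is f²·N·m/(1 + (m − 1)ρ) for the between-group effect and f²·N·m/(1 − ρ) for group by time.

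| Routine | Total N at ρ = 0.5 | ρ at which N = 138 gives 80% |
|---|---|---|
| Between groups | 236 | about 0.09 |
| Group by time, univariate | 74 | about 0.04 |
| Group by time, MANOVA | 76 | about 0.05 |

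*Reading B: d = 0.30 is the true difference at follow-up, tested by group by time.* With differences of (0, 0.30, 0.30) at the three visits, the deviations from their mean of 0.20 are (−0.20, 0.10, 0.10). Each group carries half, so f = √[(0.10² + 0.05² + 0.05²)/3] = 0.071. The univariate group-by-time routine then needs a total of 324 at ρ = 0.5, 196 at 0.7 and 130 at 0.8, and 138 gives 80% at ρ of about 0.79. With the difference growing as (0, 0.15, 0.30), f = 0.061 and the correlation is about 0.84.

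The implied correlation therefore runs from about 0.04 to about 0.84, depending on choices that the article does not report.

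**The case against.** The best defence is that neither slip harms the trial. The 81 is too large rather than too small, so at 10% loss more patients would be evaluable than required. Power of 0.80 is stated outright, which makes the 0.08 look like a misprint. No test, endpoint or decision rule uses either number. All of this stands and limits how serious the point is. It does not make the paragraph correct: a stated recruitment target should follow from the stated inputs.

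A reader might go further and infer that 80% power requires a within-patient correlation near 0.8, so that the trial is underpowered. The document does not support that. The value of 0.8 belongs to Reading B, which fixes a pattern of means and a correlation structure that the article does not state. Under Reading A, 138 arises at a correlation below 0.1, and at 0.5 the group-by-time routine needs only 74. It can fairly be said that a correlation near zero between repeats of the same test would be surprising, and that f = 0.15 in a group-by-time test means a follow-up difference of 0.64 SD (0.30 × 0.15/0.0707) rather than 0.30. That shows why the reading matters. It does not show which one was used, and a condensed article may leave this detail to the full protocol.

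Nor can the reliability figures settle it. For the Rivermead test the article says "The RBMT has reliability coefficients ranging from 0.57 to 0.86", but it does not tie the lower value to the two subtests used, and the Category fluency section gives retest values of 0.82 and 0.96. Taking 0.57 as a ceiling on the correlation would be selective.

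Finally, a reader might call 10% contradicted by the Discussion. The limitation listed there carries no number, so this is at most a tension.

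**Conclusion.** Two errors stand, and neither needs an assumption beyond the printed figures. Inflating 69 per group for 10% dropout gives 77 (76 by simple multiplication), not 81, and 81 corresponds to 14.8% loss. Beta for power of 0.80 is 0.20, not 0.08. The first enlarges the target by 4 per group and costs no power; the second is probably typographical.

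The 138 is a secondary note. It is uncheckable as printed, not shown to be wrong, and the 80% power is conditional on an unstated reading of d and an unstated correlation. No conclusion that the trial is underpowered follows.

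**What to change.** In the Sample size section:

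- Correct beta to 0.20.
- Reconcile the target and the dropout rate: either state 77 per group (154 in total) for 10% dropout, or keep 81 per group (162 in total) and state that it allows for about 15%. The second leaves the recruitment target as it is and sits better with the attrition concern in the Discussion.
- If the full protocol or analysis plan holds them, add a sentence giving the G*Power routine, the effect tested, the conversion of d = 0.30 to f and the assumed correlation, so that 138 can be reproduced. If the correlation was a guess, give power over a range of it.

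The cost is rewording one paragraph. Keeping 81 changes nothing in recruitment, and choosing 77 lowers the target by 8 in total. No extra enrolment is needed. The one drawback is that the 80% may look less secure once its conditions are stated.
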